#### Group allocation

For participants who meet inclusionary criteria following the eligibility assessment, group allocation will be specified by the study statistician using a computer-generated random number list. The group assignments will be put into sequentially numbered, opaque, sealed envelopes with the specified group number indicated inside the envelope. This will help to conceal the randomization sequence until group assignments are made. The study statistician will generate confidential treatment assignments for participants 1 through 30 and participants will receive their group assignment in the order in which they are enrolled in the treatment phase. After 30 participants are enrolled, we will conduct preliminary group comparisons of participant demographics to determine the extent that the groups are balanced. If there are statistically significant differences between groups on potentially confounding demographic variables such as age, language ability, or speech severity, we will attempt to rebalance the groups for the subsequent 30 participants who are enrolled. Speech severity will be established through combined analysis of scores from dynamic motor speech skill assessment (DEMSS) and single word articulation testing (*GFTA-3*). In cases where a participant withdraws prior to the completion of the study, the next participant to enroll will be assigned to the same treatment condition to be the substitute. Participants and clinicians will be told which group each participant is assigned to by the research team after the informed consent document has been signed and eligibility has been determined by the eligibility assessments.

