#### Stimuli

Stimuli will consist of individualized treatment targets that will be included in treatment sessions and a generalization corpus containing a common set of words that all children will produce. Treatment targets will consist of 20 words or phrases that may be targeted over the course of treatment. They will be selected by evaluating each child’s performance across assessment tasks, including their phonetic inventory, word shape inventory, lexical stress patterns, individual error profile with a specific focus on vowel errors, and responses to clinician cueing within dynamic assessment tasks (e.g., *DEMSS*). In addition, the child and/or their family will be consulted to ensure that potential treatment items are highly functional and motivating to the greatest extent possible. Targeted areas will include accuracy of movement gestures in a range of syllable and word shapes, vowel accuracy, coarticulatory contexts including a range of consonant and vowel transitions, and varied stress patterns.

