The generalization corpus will be used to examine carryover of treatment gains. This set of words/phrases consists of 45 words/phrases that will not be included in treatment for any participant. These words/phrases have been divided into 15 low complexity targets, 15 medium complexity targets, and 15 high complexity targets. Target complexity was determined according to word structure, segmental features, and lexical/phrasal stress. Word structure of targets follows a hierarchy of increasing complexity determined by syllable/word shape (e.g., CV, VC, CVC, CVCV, VCVC, CCVC, CVCVC, etc.), syllable number (e.g., monosyllabic, bisyllabic, multisyllabic words and phrases), and presence of adjacent consonants (e.g., CCVC; CVC CVC). Segmental complexity accounts for age of acquisition (i.e., Early 8, Mid 8, Late 8; [50]), consonant features (i.e., place, manner, voicing), and vowel characteristics (i.e., vowel height/advancement; monophthong, diphthong). Complexity of movement transitions considers whether targets contain the same or different consonant–vowel sequences (i.e., same consonants/vowels, varied consonants/same vowels, same consonant/varied vowels, varied consonants/varied vowels) and the extent of place/manner/voicing changes across phoneme sequences. Suprasegmental complexity is based on whether lexical and phrasal stress follows either a trochaic or iambic pattern. See Table 1 for details regarding each level of complexity. Children with severe CAS will produce the 30 low and medium complexity targets. Those with moderate CAS will produce the 30 medium and high complexity targets. The child’s complexity level will be determined from their initial speech assessments using a checklist that clinicians will complete. The 15 medium complexity non-treatment words will be elicited from all participants.

**Table 1 Tab1:** Target complexity framework

	**Word Structure**	**Segmental Complexity**	**Movement Sequences**	**Lexical Stress**
**Low Complexity**	CV VC CVC Reduplicated CVCV	**Consonants** Early consonants **Vowels** Simple vowels, diphtongs	Same consonant/vowel sequences	Trochaic
**Medium Complexity**	CVC CVCV VCVC	**Consonants** Early, mid, and some late consonants; Homorganic consonant clusters **Vowels** Simple vowels, diphthongs	Same and varied combinations of consonants (differing by place, manner, and/or voicing) and vowels	Mostly trochaic, some iambic

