#### Probe data

Treatment outcomes will be measured using probe data, which will be collected before, during, and following the intervention phase. The data collection schedule is presented in Table 2. Probe words consist of 50 items that include 20 individualized potential treatment targets and a 30-item generalization corpus. At each data collection session, one list of probe words will be presented in a randomized order with each word produced once. Probe data will be elicited in direct imitation (e.g., “Say, “apple") with no feedback or cues provided. The procedure for probe data collection is identical in baseline, treatment, and follow-up phases.

**Table 2 Tab2:** Data collection schedule

	**Low dose frequency**			**High dose frequency**		
**Study week**	***Treatment***	***Assessment***	***Assessment evaluates***	***Treatment***	***Assessment***	***Assessment evaluates***
-3 to -2		P1 (× 1), ICS, FOCUS 34	Baseline accuracy, intelligibility and participation		P1 (× 1), ICS, FOCUS 34	Baseline accuracy, intelligibility and participation
-1		P2 (× 3)			P2 (× 3)	
1	Tx1 Tx2	P3 (× 1)	Baseline accuracy (pre-Tx1)	Tx1 Tx2 Tx3 Tx4	P3 (× 1)	
2	Tx3 Tx4	-		Tx5 Tx6 Tx7 Tx8	P4 (× 1)	Accuracy after 6 Tx sessions (pre-Tx7)
3	Tx5 Tx6	-		Tx9 Tx10 Tx11 Tx12	-	
4	Tx7 Tx8	P4 (× 1)	Accuracy after 6 Tx sessions (pre-Tx7)	Tx13 Tx14 Tx15 Tx16	P5 (× 1)	Accuracy after 12 Tx sessions (pre-Tx13)
5	Tx9 Tx10	-		Tx17 Tx18 Tx19 Tx20	P6 (× 1)	Accuracy after 18 Tx sessions (pre-Tx19)
6	Tx11 Tx12	-		Tx21 Tx22 Tx23 Tx24	P7 (× 2), ICS, FOCUS 34	Accuracy after 24 Tx sessions (1-day post-Tx24), intelligibility and participation
7	Tx13 Tx14	P5 (× 1)	Accuracy after 12 Tx sessions (pre-Tx7)		P8 (× 3)	1-week post-Tx accuracy
8	Tx15 Tx16	-				
9	Tx17 Tx18	-				
10	Tx19 Tx20	P6 (× 1)	Accuracy after 18 Tx sessions (pre-Tx19)		P9 (× 2), ICS, FOCUS 34	4-week post-Tx accuracy, intelligibility and participation
11	Tx21 Tx22	-				
12	Tx23 Tx24	P7 (× 2), ICS, FOCUS 34	Accuracy after 24 Tx sessions (1-day post-Tx24), intelligibility and participation			
13		P8 (× 3)	1-week post-Tx accuracy			
16		P9(× 2), ICS, FOCUS 34	4-week post-Tx accuracy, intelligibility and participation			
18					P10 (× 3)	12-week post-Tx accuracy
24		P10 (× 3)	12-week post-Tx accuracy			

*P* Probe session, *ICS* Intelligibility in Context Scale [29], *FOCUS 34* Focus on Communication in Under Six [30], *Tx* Treatment

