This study will compare two different treatment schedules and, consequently, it is imperative that children attend according to the prescribed schedule. While missing sessions due to illness such as COVID-19 cannot be avoided, it is possible to schedule study participation around other commitments such as vacations and holidays. To avoid preventable absences from treatment and follow-up sessions and ensure adherence to the study protocol, each clinician will work through the entirety of the study schedule with families prior to conducting baseline testing. Families will sign off in agreement to all dates from baseline through the 12-week follow-up before these activities begin.

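### As written, clinicians and families appear to know the arm before the baseline probes, and no stated step closes the 20 child-specific outcome words before that

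*Protocol article*

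**What the plan says.** All references are to the protocol article.

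- **Disclosure.** Group allocation: clinicians and families "will be told which group each participant is assigned to by the research team after the informed consent document has been signed and eligibility" is settled. Disclosure is not tied to any later step, such as completion of the word list or of baseline probes.
- **Scheduling.** Potential limitations: "each clinician will work through the entirety of the study schedule with families prior to conducting baseline testing". It continues: "Families will sign off in agreement to all dates from baseline through the 12-week follow-up before these activities begin".
- **Choice of words.** Stimuli: "Treatment targets will consist of 20 words or phrases that may be targeted over the course of treatment". They are selected from the child's assessment results and response to cueing, and "the child and/or their family will be consulted to ensure that potential treatment items are highly functional and motivating" as far as possible. The section does not say who makes the final choice, whether that person is blind to arm, or when the list closes.
- **Role in the outcome.** Probe data: "Probe words consist of 50 items that include 20 individualized potential treatment targets and a 30-item generalization corpus". Outcome measures applies the MACS, the primary outcome, to both sets of items.
- **Complexity level of the corpus.** Stimuli: this is "determined from their initial speech assessments using a checklist that clinicians will complete".
- **Safeguards.** Allocation is by sealed envelope (Group allocation). Probes are elicited by direct imitation without cues or feedback (Probe data). Research assistants who transcribe and score do not know group or time point (Data preparation).

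**The concern.** Randomization balances what is fixed before the arm is known. It cannot balance choices made afterwards. Here part of the measuring instrument is built separately for each child, by judgement and with family input. The difficulty of the chosen words sets the starting score and the room for gain. If a clinician or family who already knows the schedule leans, even unintentionally, towards a different kind of word, the arms differ in what is measured and not only in how the children respond.

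The baseline raises a related issue. Gains are calculated from baseline, and the baseline probes are elicited by community clinicians who, on this sequence, already know the arm. Expectations are not neutral: the Current study section predicts an advantage for the high-frequency group at six weeks and in maintenance.

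A third consequence is early loss. Potential limitations foresees that some families will find four visits a week too much and that others will prefer it. A family that learns its arm and leaves before P1 provides no baseline probe at all.

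**Working it through.** The question is one of sequence, so the check sets the sections side by side. The only arithmetic is counting.

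**1. When is the arm known?** Group allocation gives only the earliest time: after consent and eligibility. Potential limitations supplies the latest: all dates through the 12-week follow-up are agreed before baseline activities begin. Table 2 shows that no single calendar fits both arms:

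| Event | High frequency | Low frequency |
|---|---|---|
| Last treatment session | week 6 | week 12 |
| P9 (4 weeks post) | week 10 | week 16 |
| P10 (12 weeks post) | week 18 | week 24 |

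A family that has signed one full set of dates therefore knows its arm, and so does the clinician who worked through it with them. The implied order is: consent, eligibility, disclosure, signed calendar, P1, P2, P3, session 1.

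**2. How much of the baseline follows disclosure?** The baseline phase has P1 once, P2 three times and P3 once: 1 + 3 + 1 = 5 probe sets. On the implied order, all five come after disclosure.

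**3. How much of the outcome is child-specific?** 20 / 50 = 40% of the items in every probe, and every item from which a treated-word score can be formed.

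**4. Is the list closed before disclosure?** It must exist by P1, because every probe contains it. Under step 1, however, disclosure has also happened by P1. The assessments that inform the list precede disclosure, but the family consultation and the final choice have no stated date.

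**5. How exposed are the other 30 items?** Much less. The corpus is fixed. Every child produces the 15 medium-complexity items, so at most 30 − 15 = 15 items vary between children, according to a level derived from the initial assessments.

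**6. Do the safeguards cover the gap?** Sealed envelopes protect assignment, blinded scoring protects rating, and uncued imitation limits influence during elicitation. None of them governs which words are chosen or stops a family leaving once the arm is known.

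**7. Can the bias be sized?** No. The documents give no variability for the MACS gain and nothing about how word choice might shift with schedule.

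**The case against.** **The order is inferred.** This stands in part. The scheduling text sits in a limitations section, concerns absences and never mentions allocation. Table 2 pairs P1 with the ICS and FOCUS-34, which Assessment procedure lists within the eligibility assessment, so P1 could be read as falling before disclosure, with the list already fixed. Signing all dates before baseline still points the other way. A reader might take the article to state outright that disclosure precedes P1; it implies this strongly but does not say it.

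**This is silence in a condensed article.** A study manual is mentioned and may fix when the list closes. That would answer the word-choice point. It would not answer baseline collection after disclosure, which follows from what the article does say.

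**No mechanism is shown.** Both arms receive 24 one-hour sessions, five active targets and the same graduation rule, and nothing suggests that either schedule calls for easier or harder words. This is fair. The point is that the design leaves the route open, not that bias has been shown.

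**The whole probe is compromised.** A reader might infer this because clinicians complete the complexity checklist. The documents do not support it: the level comes from the initial assessments, and half of the 30 corpus items are common to all children.

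**Reordering would rescue the intention-to-treat analysis.** A reader might infer this too. It would not: a child who leaves before treatment has no post-treatment outcome in either case. Such children also already have eligibility measures, including the GFTA-3 and DEMSS. Earlier P1 and P2 would add baseline probe data on early leavers and might reduce their number.

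**Clinicians would still know the arm later.** True. P4 to P10 and P3 would be elicited with the arm known under either order.

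**Conclusion.** The concern holds as a weakness in the order of steps. Read together, Group allocation, Potential limitations and Table 2 place all five baseline probe sets after clinicians and families know the arm. No stated step closes the 20 discretionary words, 40% of the primary-outcome items, before that point. Item choice and the elicited baseline could therefore depend on arm.

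This rests on two readings: that the dates families sign are those of one arm, and that no document outside the article closes the list earlier. Direction and size are unknown. A reader might want to express the risk as a share of the planned effect of 0.35, but that would need an invented shift and an invented standard deviation. The 0.35 is also standardised by the model variance, so a shift divided by the SD of gain would not be on the same scale. The change is worth making because the exposure touches the primary outcome and is cheap to remove, not because a particular bias has been demonstrated.

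**What to change.** Reorder steps that already exist:

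1. After eligibility is confirmed, finalise and date-stamp the 20-word list, and record the complexity level already derived from the initial assessments.
2. Have families agree provisional dates for both schedules.
3. Collect P1 and P2, with the baseline ICS and FOCUS-34.
4. Only then open the envelope, disclose the arm and confirm the matching calendar.
5. Leave P3 immediately before session 1.

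This makes the outcome items and four of the five baseline probe sets (1 + 3) independent of knowledge of the arm. It needs no extra visits or participants. The cost is that families and clinicians hold two provisional calendars for about two weeks. If the list is already closed before disclosure in practice, the article should say so; disclosure would still need to move after P2.

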### Intervention delivery and dosage

DTTC treatment will be administered on an individualized basis by SLPs who were trained in DTTC by the research team, as described below. Treatment will take place in clinic rooms or at the child’s home in a quiet space. Treatment addressing functional communication, language goals, and the like will be allowed over this time period. Participants will receive 24 h of treatment, provided at no cost to the family. All sessions will be audio and video recorded for reliability and scoring purposes. We will report the number of participants initially recruited and tested, as well as those who did or did not meet inclusionary criteria in publications and presentations.

#### DTTC protocol

Participants in both conditions will receive DTTC treatment. In DTTC treatment, the target is accurate speech movement gestures in production of real words or phrases, rather than targeting accurate individual speech sounds as is common in traditional approaches for speech sound disorders [9]. Words and/or phrases are selected on an individual basis to target specific speech movement patterns and to be functional and motivating for each child (see Stimuli section below).

In DTTC, treatment targets are practiced along a temporal-based production hierarchy to provide varying degrees of support to facilitate speech accuracy [9]. Levels of the hierarchy include: (1) *Simultaneous Production –* the child and clinician produce targets at the same time*,* (2) *Direct Imitation –* the child produces the target immediately following the clinician’s model*,* (3) *Delayed Imitation –* the child produces the target following a brief delay after the clinician’s model*,* (4) *Spontaneous Production –* the child produces the target in response to questions or phrases. At lower levels of the hierarchy (i.e., *Simultaneous Production*, *Direct Imitation*), words are initially practiced at a reduced rate of speech to allow more time for the planning/programming of speech movements; practice gradually moves towards a regular rate as the child gains accuracy. Furthermore, prior to advancing along the temporal hierarchy, treatment targets are practiced while varying prosody (i.e., producing a target *happy/sad/mad/loud/soft/in a question*) to introduce practice variability and promote greater speech motor learning. Based on the individual needs of the child, the clinician provides multisensory cues (e.g., verbal, visual, tactile, gestural cues) to support production accuracy combined with frequent, specific feedback related to movement accuracy (i.e., knowledge of performance feedback). As the child becomes more accurate, clinician support and feedback are faded to only indicate accuracy of productions (i.e., knowledge of results feedback) and feedback is provided at a lower frequency.

During DTTC treatment sessions, a small set of treatment targets are practiced using a modified block schedule. A total of five words or phrases (i.e., treatment targets) will be practiced within any given treatment session with one treatment target produced individually at a time in either a small block (i.e., 15–24 words per block) or a large block (i.e., 25–40 words per block). The objective of each session is to achieve 2–3 blocks for each treatment target. There is a minimum of 50 productions per session required for each participant although we anticipate that there will be between 100–200 productions per session for each participant. In each session the clinicians will practice 5 treatment targets with 2–3 blocks per targeted word/phrase (total of 10–15 blocks across the session) with small blocks containing 15–25 productions and large blocks containing 25–40 productions. Clinicians will record each time a target was practiced and whether it was practiced in a small or large block.

At the beginning of each block, the clinician elicits a target in direct imitation and then uses clinical decision-making to determine the appropriate level of the temporal hierarchy depending on the degree of support needed for the targeted word/phrase (most support = *Simultaneous;* least support = *Spontaneous*). Practice may advance from *Simultaneous Production* to *Direct Imitation* once the child has accurately produced a treatment target 5–15 times at a regular rate of speech and the clinician has introduced varied prosody. After achieving 5–15 accurate productions at *Direct Imitation* with varied prosody, a target will be practiced at the level of *Delayed Imitation*. Practice will advance from *Delayed Imitation* to *Spontaneous Production* once a child has accurately produced a target 10–15 times with varied prosody. Once a word/phrase has been accurately produced at the level of *Spontaneous Production* 10/10 times across three consecutive sessions, that treatment target will be graduated out of active practice. The clinician will then refer to the Treatment Target bank to determine the next word or phrase item to include in treatment.

Dynamic assessment will be used to evaluate whether a word or phrase is ready for active treatment (e.g., stimulable with clinician support) and an appropriate substitute for graduated treatment targets. At the end of a treatment session during which a target has been graduated out of active practice, the clinician will select one word/phrase from the set of 20 potential treatment targets and briefly practice this target with the child. If the child responds to clinician cueing (e.g., verbal, tactile, visual, temporal cues), this word/phrase will be added to active treatment. If a child repeatedly attempts a word/phrase but productions remain equally inaccurate despite clinician cues, that target will not be introduced to treatment and the process will be repeated with a different word/phrase.

#### Clinicians

Community clinicians will be recruited to administer the assessment and treatment protocols. We anticipate having up to 35 different community clinicians across North America who practice in community clinics, schools, and private practice, primarily in the continental United States. Clinicians will undergo a rigorous application and training process including completion of 20 h of didactic and applied learning modules focused on assessment, treatment, research ethics, and study-specific protocols. Following the training and prior to collecting data, clinicians will achieve 90% fidelity in administration of the DEMSS and DTTC, achieve 90% accuracy or higher on an examination that assesses knowledge of the RCT’s experimental protocols and procedures, and achieve 90% reliability in making perceptual judgments of segmental and prosodic accuracy.

